#### Exclusion criteria

Participants meeting one or more of the following criteria are excluded:

1. Bipolar depression, treatment-resistant depression, and severe suicidal risk;

2. History of bipolar disorder, schizophrenia, obvious psychotic symptoms, and depression disorder caused by non-addictive substances;

3. Combine with severe cardiovascular diseases, cerebrovascular diseases, hepatic diseases, renal diseases, hematological disease, cancer, or other severe primary diseases;

4. Pregnant or lactating women;

5. Inability to finish the compliance test, judge the efficacy, and have complete data;

6. Involved with any other clinical trial at the time of consent.

#### Who will take informed consent? {26a}

All participants with depression enrolled in the study as well as 36 healthy people sign a paper version of informed consent prior to study initiation. The recruitment of participants in each study centre is made by the researchers (doctors) in each study center. Researchers make face-to-face evaluation of patients or healthy people who are willing to participate in the project. If the participants meet inclusion criteria, the researchers inform them to sign the informed consent. Only after signing the informed consent can the trial process be officially started. Two copies of the informed consent were kept by the researchers and the participants, respectively.

#### Additional consent provisions for collection and use of participant data and biological specimens {26b}

Standard clinical laboratory findings (including complete the blood count, liver, and kidney function tests) as indicators of safety evaluation are routinely collected before and after the enrollment of patients to ensure the safety of subjects. Participants’ urine samples and blood samples are monitored by liquid chromatography-mass spectrometry (LC-MS) technology to explore the mechanism of action of the metyrapone at baseline and at 4 weeks. At the same time, participants’ blood samples are used to separate the total RNA. The study participants have given consent for their blood samples and data to be used. The ethics committee has given consent to the trialists to conduct the study. All the samples required for the study do not need to sign additional informed consent, because the committee has already been approved by the ethics committee and can use the data after signing the informed consent.

### Interventions

#### Explanation for the choice of comparators {6b}

The placebos were manufactured by the Jiuzhitang Co., Ltd. Placebos are similar to the physical traits of Xiaoyao pills in size, flavor, scent, and color without the key ingredients. The placebos are composed of corn starch, pregelatinized starch, maltose, caramel color, and water.

### Intervention description {11a}

Participants randomized to treatment Group 1 take Xiaoyao pills, which are composed of ChaiHu (Radix Bupleuri)-100g, DangGui (Radix Angelicae Sinensis)-100g, BaiShao (Radix Paeoniae Alba)-100g, BoHe (Mentha)-20g, ShengJiang (Ginger)-100g, BaiZhu (Atractylodes macrocephala Koidz) - 100 g, FuLing (Poria cocos Wolf) -100g, and ZhiGanCao (Glycyrrhiza uralensis Fisch)-80g. The action and batch number of each herb are summarized in Table 1. Xiaoyao pills are water honey pills (Z20013060) manufactured by the Jiuzhitang Co., Ltd. Participants in Group 2 take placebos which are manufactured by the Jiuzhitang Co., Ltd. Placebos are similar to the physical traits of Xiaoyao pills in size, flavor, scent, and color without the key ingredients. The placebos are composed of corn starch, pregelatinized starch, maltose, caramel color, and water. Participants are required to take the medicine twice daily for four consecutive weeks and the dosage is 9g twice a day. The normal group are not given any drug.

**Table 1 Tab1:** The action and batch number of each herb

Ingredients	Lot number	Action
***BaiZhu*** ***(Atractylodes*** ***Macrocephala Koidz)***	018AJ-2005005-725	TCM: Tonifying *Qi* of the spleen, eliminating dampness, and diuresis.
***Chaihu*** ***(Radix Bupleuri)***	FM201538	TCM: Soothing the liver and tonifying qi, relieving depression, and reducing fever. Pharmaceutical study: (1) sedative effect. (2) analgesic effect. (3) Anti-pathogen effect.
***Danggui*** ***(Radix Angelicae Sinensis)***	FM201541	TCM: Moisturizing the intestines promoting blood circulation and removing blood stasis, regulating menstruation, and relieving pain.
***Baishao*** ***(Radix Paeoniae alba)***	FM201030 FM201037 FM201041	TCM: Restraining yin and stopping sweating, nourishing blood and regulating menstruation, calming liver yang, softening liver, and relieving pain.
***Fuling*** ***(Poria cocos Wolf)***	FM201540	TCM: Diuresis, detumescence, tonifying *Qi* of the spleen, and tranquilization. Pharmaceutical study: (1) Diuresis effect. (2) Calming effect. (3) Anti-tumor effect. (4) Anti-diabetic effect. (5) Enhance myocardial contractility.
***Zhigancao*** ***(Glycyrrhiza uralensis Fisch)***	FM200983	TCM: Tonifying *Qi* of the spleen, eliminating phlegm, anti-cough, heat-clearing and detoxifying, and reconciling. Pharmaceutical study: (1) Anti-arrhythmia effect. (2) Anti-ulcer effect. (3) Diuresis effect. (4) Analgesia effect. (5) Anti-tussive effect. (6) Eliminating phlegm effect.
***Bohe*** ***(Mentha)***	FM201542	TCM: Evacuating wind-heat, clearing the boss, relieving the throat, clearing the rash, soothing the liver, and promoting qi. Pharmaceutical study: (1) Anti-inflammatory effect. (2) Sedative effect. (3) Choleretic effect. (4) Penetration promoting effect.
***Shengjiang*** ***(Ginger)***	FM201539	TCM: Relieving the appearance and dispelling cold, warming the middle to stop vomiting, warming the lungs and detoxifying. Pharmaceutical study: (1) Antibacterial effect. (2) Anti-cancer effect. (3) Anti-oxidation effect. (4) Anti-aging effects.

### Criteria for discontinuing or modifying allocated interventions {11b}

#### Shedding criteria

Cases that have been enrolled but do not complete the clinical protocol should be considered drop outs in the following circumstances:

1. Patients withdrew from the trial on their own;

2. Lost to follow-up;

3. Poor compliance;

4. Because some diseases are considered by the study physician to be amenable to withdrawal from the trial.

The case should be explained. If the baseline pharmacodynamic data are available, the results of the last major outcome can be transferred to the final result for statistical analysis, and the research records should be kept for reference.

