#### Procedure for unblinding if needed {17b}

At the end of the trial, the first-level uncovering blinding is performed after checking CRF, EDC, and signature. The groups of subjects are determined by the first-level uncovering blinding to conduct statistical analysis. After the statistics analysis, the second-level uncovering blinding is performed. Through the second-level blinding, the Xiaoyao pill group and the placebo group are determined to evaluate the drug efficacy. Unblinding is generally done at the end of the trial for statistical analysis and outcome assessment. However, in order to ensure the safety of the subjects, the blindness is uncovered in some emergency situations, such as the occurrence of a serious adverse event, unable to judge its relationship with the trial drug, whether it is overdosed, whether it has serious drug interactions with the concomitant medication, etc. When it is urgent, researchers need to know what drug to take to decide the rescue regimen. After uncovering blindness, it is necessary to record the time, reason for breaking the blindness in advance and the person performing the blind breaking, and to notify the inspector and the sponsor as soon as possible. Once the blindness is uncovered in advance, the participants should not continue to participate in the study. The data of these participants cannot be used for the efficacy evaluation analysis, but the data should still be included in the safety analysis data set. And the participants should be treated and protected in time. An emergency letter is prepared for every participant with an envelope made of thick, light tight paper. Unblinding of a single participant should not disrupt the blinding of the entire clinical trial. Emergency letters are made by a third-party person unrelated to this trial.

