#### Plans to promote participant retention and complete follow-up {18b}

A participant follow-up record form is set up for this study, and the follow-up of participants is managed by the clinical research coordinator (CRC). Clinical research coordinators record patients’ enrollment time, follow-up time, dose of drug, and remaining dose of drug at every follow-up time. Clinical research coordinators contact the participants to go to hospital on the follow-up day, and the research doctors evaluate the patient on the follow-up day and distribute drugs of the next phase. Every time the participants go to the hospital, they receive appropriate transportation subsidy. Before joining the project, the patient is promised to receive further treatment guidance from a specialist after the trial. If the subjects drop out of the trial or interrupt the trial, the data of the subjects is blinded with other subjects until the trial is completed. And the data of these subjects is statistically analyzed separately before uncovering blindness and finally are explained separately in the outcome part of this trial.

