#### Adverse event reporting and harms {22}

Once an adverse event occurs, the investigator shall state to the subject that the subject is required to report truthfully the changes in his condition following the medication. Physicians are to avoid inducing questions.While observing efficacy, pay close attention to observing adverse events or unanticipated toxic side effects (including symptoms, signs, laboratory tests), analyze the causes, make judgment, and follow-up observations and records.For adverse events occurring during the study period, their symptoms, extent, time of appearance, duration, handling measures, experience, etc. should be recorded on a case report form, evaluated their relevance to the study drug, and recorded in detail by the investigator, signed, and dated.When an adverse event is identified, the observing physician may decide whether to discontinue observation based on the condition, and cases who discontinue because of adverse effects should be followed up with a detailed record of the handling and outcome.In the event of a serious adverse event in a study, the unit that assumes the responsibility for the clinical study must take immediate measures to protect the safety of subjects, must report to the project leader and the Research Center for clinical trials of drugs, should report within 24 h to the drug administration, the subject responsible unit, and the ethics committee. The investigator should also report to the data monitoring committee and relevant regulatory bodies as required indicating expectedness, seriousness, severity, and causality.Investigator should sign and date on report. The subject responsible unit will guarantee reporting procedures that meet all legal and regulatory requirements.When urgent breaking of blinding is required for a serious adverse event to occur in a clinical study, the blinding should be broken jointly by the project leader, investigator, clinical monitor.

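### Poor compliance, physician withdrawal, emergency unblinding and, at the physician's discretion, adverse events are tied to leaving the trial or ending observation, and outcome assessment is not kept separate from study treatment

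*Protocol article*

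**What the plan says.** All references are to the protocol article.

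- **Shedding criteria, section {11b}.** The rule is "Cases that have been enrolled but do not complete the clinical protocol should be considered drop outs in the following circumstances". The four circumstances are the patient's own withdrawal, loss to follow-up, "Poor compliance", and withdrawal that the study physician considers warranted by some disease. If baseline data exist, "the results of the last major outcome can be transferred to the final result for statistical analysis".
- **Unblinding, section {17b}.** "Once the blindness is uncovered in advance, the participants should not continue to participate in the study". It adds: "The data of these participants cannot be used for the efficacy evaluation analysis". These patients stay in the safety data set.
- **Adverse events, section {22}.** When an event is identified, "the observing physician may decide whether to discontinue observation based on the condition". It also says that "cases who discontinue because of adverse effects should be followed up with a detailed record of the handling and outcome". Neither HAMD nor the TCM scale is named.
- **Retention, section {18b}.** Coordinators call participants in on follow-up days, doctors evaluate them, and the record includes "dose of drug, and remaining dose of drug at every follow-up time". Data from those who drop out or interrupt are analysed and explained separately.
- **Specimens, section {33}.** Blood and urine tests are repeated on exit. No HAMD is mentioned there.
- **Missing data, section {20c}.** Participants without primary or secondary outcome data are left out.
- **Outcomes, section {12}.** HAMD is scored at baseline and weeks 1, 2 and 4.

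**The concern.** Section {11b} is about discontinuing or modifying the intervention, but its Shedding criteria answer with drop-out from the trial. The first two circumstances already cover patients who have left or cannot be found. The third and fourth therefore add patients who may still be attending. Poor compliance can come to light through the count of remaining drug at a visit that the patient attends.

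Poor adherence, adverse events and physician withdrawal can all be related to lack of benefit or to tolerability, so their frequency may differ between Xiaoyao pills and placebo. If assessment stops with treatment, the collection rule itself produces informative missing data on the primary outcome. Analyses that use the week-1 and week-2 scores can help, but only under assumptions that cannot be tested. Resolving the separate conflict between carry-forward in {11b} and exclusion in {20c} would not supply scores that were never taken.

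**Working it through.** **1. The triggers side by side**

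| Trigger | What the text does | Week-4 HAMD |
|---|---|---|
| Poor compliance; physician withdrawal ({11b}) | Classed as drop-out; last outcome may be carried forward | Loss implied, not ordered |
| Emergency unblinding ({17b}) | Participation ends; efficacy data barred | Loss explicit in effect |
| Adverse event ({22}) | Physician may end observation; event followed up | Loss possible, case by case |
| Stopping the pills, nothing else | No rule stated | Not addressed |

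Carrying the last value forward makes sense only where no final value is expected. This is why the loss is implied for the first row. No section shown states that patients in the first three rows keep their HAMD visits.

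**2. The plan's own figure**

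Section {14} gives 30 per arm and 15% dropout. 30 / (1 − 0.15) = 35.3, rounded up to 36 per arm, so 72. The stated total is reproduced.

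**3. How many patients**

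0.15 × 72 = 10.8, about 11. This is a ceiling: it includes voluntary withdrawal and loss to follow-up, which no change in wording can retain. The article does not split dropout by reason.

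**4. Size if the last value is carried forward**

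The assumptions, none of them in the article, are: stops occur after week 1; 5 HAMD points of change would still follow by week 4 in both arms, even off drug; SD 6.

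- SE of the difference = 6 × √(2/36) = 1.41.
- Shift = gap in stopping rate × remaining change.
- Stopping 20% v 10% (7.2 + 3.6 = 10.8 patients, the whole allowance): 0.10 × 5 = 0.5 points, or 0.5/1.41 = 0.35 SE.
- Stopping 25% v 5% (9.0 + 1.8 = 10.8 patients): 0.20 × 5 = 1.0 point, or 1.0/1.41 = 0.7 SE.
- If only 2 points of change remain: 0.10 × 2 = 0.2 and 0.20 × 2 = 0.4 points.

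**5. Size if the patient is excluded**

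The formula in step 4 does not apply here. If a share m of one arm is unassessed and would differ from completers by d points, that arm's mean is off by m × d. With m = 0.15 and d assumed at 2 to 6 points, this is 0.15 × 2 = 0.3 to 0.15 × 6 = 0.9 points. The bias in the comparison is m₁d₁ − m₂d₂, which is zero if both arms lose the same share of the same kind of patient.

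**The case against.** The strongest case is that a reader might infer that every stop of the pills, every poorly compliant patient and every adverse event ends assessment. The article does not support that.

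- No section says that stopping the pills alone ends participation or assessment.
- After an adverse event, ending observation is a decision for the physician, not automatic.
- The Shedding criteria label cases that did not complete the protocol. They do not forbid a week-4 visit, and {18b} has coordinators calling participants in.

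All three stand and set the limits of the point.

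A reader might also infer that safety data are lost. They are largely provided for: {22} follows adverse-effect discontinuations, {33} repeats laboratory tests at exit, and {17b} keeps unblinded patients in the safety set.

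The magnitude rests on assumed values, and the carry-forward calculation charges the whole 15% allowance to the problem. That also stands, so the figures indicate scale only. Emergency unblinding is confined to emergencies, and the article gives no expected number.

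Finally, this is a condensed article whose schedule figure is not shown, and the full protocol may retain off-treatment patients. That weakens any complaint about silence. It does not remove the rules that are printed, namely drop-out status for poor compliance, an end to participation after unblinding, and discretion to end observation. If the full protocol differs, these sentences need to be aligned with it.

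**Conclusion.** The point holds in limited form. The protocol does not separate ending study treatment from ending outcome assessment, and its stated rules allow reachable, consenting patients to have no week-4 HAMD. The loss is explicit in effect after emergency unblinding, implied after poor compliance or physician withdrawal, and discretionary after an adverse event.

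The consequence is avoidable and possibly informative missing data, which bias the primary comparison only if the losses differ by arm in number or kind. At most about 11 of 72 patients fall within the allowance, and an unknown smaller number could be retained. The range of roughly 0.5 to 1 HAMD point depends on 5 points of remaining change and a 10- to 20-point gap in stopping rates, and it shrinks in proportion if either is smaller. This is a modest bias that should be corrected, not one shown to overturn the result. No view is taken on when treatment should be stopped or the blind broken.

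**What to change.** The change is to data collection only; treatment decisions stay with the physician.

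1. In the Shedding criteria, reserve drop-out for withdrawal of consent and loss to follow-up. Record poor compliance and discontinuation of study treatment as separate items, with date and reason.
2. In {11b}, {17b} and {22}, state that the remaining scheduled HAMD, TCM-scale and adverse-event assessments continue unless the participant withdraws consent.
3. Reconcile this with the bar in {17b} on using unblinded participants' efficacy data; otherwise the added scores would be collected and then discarded. One option is to keep these participants in the analysis as randomised and flag scores taken after unblinding.

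**Cost.** Under {25}, an amendment needs ethics approval and written information to patients, and the Trial status section describes recruitment as ongoing. Case report forms need small changes. The extra visits are already on the schedule and concern fewer than about 11 patients, with the transport subsidy of {18b} payable at each. Some week-4 scores will be off drug and will slightly dilute the on-drug effect.

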#### Discontinuing criteria

The entire trial is completely stopped in multi-centers for the following reasons:

1. Serious safety concerns identified by the investigator;

2. There are major lapses in the trial;

3. Reasons for funding or management by the sponsor;

4. The administrative department cancels the trial.

Total discontinuation of the trial can be temporary or permanent. When discontinuing a trial, full trial records should be retained.

#### Rejection criteria

Cases that have been enrolled but meet one of the following should be removed:

1. Cases were incorrectly diagnosed and incorrectly included;

2. Met the exclusion criteria;

3. One medication was not used;

4. Without any test record;

5. Due to the use of some prohibited medication, it was not possible to evaluate drug efficacy.

Rejected cases should state the reason, and their original medical records should be retained for statistical analysis of efficacy.

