#### Methods in analysis to handle protocol non-adherence and any statistical methods to handle missing data {20c}

Participants with missing primary or secondary outcome data are excluded.

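### Randomised patients are dropped from the efficacy analysis for events after randomisation, under conflicting rules and with no analysis of all randomised patients

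*Protocol article*

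**What the plan says.** The relevant text of the protocol article is spread over five places.

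- **Rejection criteria**: "Cases that have been enrolled but meet one of the following should be removed". The list mixes entry errors (wrong diagnosis, ineligibility), no medication taken, "Without any test record", and item 5: "Due to the use of some prohibited medication, it was not possible to evaluate drug efficacy". The section closes with "Rejected cases should state the reason, and their original medical records should be retained for statistical analysis of efficacy".
- **Procedure for unblinding {17b}**: on patients whose code is broken early, "The data of these participants cannot be used for the efficacy evaluation analysis". They stop taking part but stay in the safety data set. A serious adverse event is one of several listed reasons for breaking the code.
- **Missing data {20c}**: "Participants with missing primary or secondary outcome data are excluded".
- **Shedding criteria {11b}**: for dropouts, including those with poor compliance, the last outcome may be carried forward if baseline data exist.
- **Participant retention {18b}**: data of patients who drop out or interrupt are analysed and explained separately.

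The article names a safety set. It does not name an efficacy set that contains all randomised patients.

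**The concern.** Randomisation protects the comparison of Xiaoyao pills with placebo only while patients stay in the arm to which they were assigned. Taking another medication can follow lack of response. Early unblinding can follow harm. A missed visit can follow either. All three arise after allocation and may occur at different rates, or in different kinds of patient, in the two arms. Excluding those patients compares two selected subsets, and any difference in selection is mixed into the estimated treatment effect.

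The rules also disagree with one another, so two analysts working from this text could analyse different patients. With 36 patients per arm, a handful of exclusions is enough to matter.

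**Working it through.** **1. What each rule does to a randomised patient**

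| Event after randomisation | Where | Treatment in efficacy |
|---|---|---|
| Early unblinding | {17b} | Data barred without exception, including scores already collected |
| Missing primary or secondary outcome | {20c} | Excluded; as written, a missing secondary outcome is enough |
| Prohibited medication judged to prevent assessment of efficacy | Rejection criteria, item 5 | Removed, yet "their original medical records should be retained for statistical analysis of efficacy" |
| Dropout or poor compliance | {11b}, Shedding criteria | Last outcome may be carried forward |
| Dropout or interruption | {18b} | Analysed separately |

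A patient who leaves after week 2 with no week-4 score is excluded under {20c}, may be carried forward under {11b}, and is set apart under {18b}. These cannot all describe the same analysis.

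**2. Scale of possible exclusions**

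The article gives no exclusion rate. Its dropout allowance under Sample size {14} is the nearest figure: 30/(1 − 0.15) = 35.3, rounded up to 36 per arm, or 72 in total. This reproduces the stated total. Fifteen per cent of 36 is 5.4, so about 5 patients per arm.

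**3. Illustration on a mean score**

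Assume a normal outcome and that the worst fraction q of one arm only is lost. The arm's mean moves by φ(z₁₋q)/(1 − q) standard deviations.

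- q = 0.05: 0.109 SD
- q = 0.10: 0.195 SD

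The article gives no HAMD standard deviation. At an assumed 6 points these are 6 × 0.109 = 0.65 and 6 × 0.195 = 1.17 points. At 5 points they are about 0.5 and 1.0, and at 7 points about 0.8 and 1.4. With the same outcome distribution in both arms, equal truncation would cancel in the difference, so this is a one-arm worst case.

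**4. Illustration on a response rate**

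Assume no true effect, response rate r in both arms, a fraction d of the active arm excluded (all non-responders), and the same fraction of placebo excluded at random. The apparent active rate is r/(1 − d). The type I error is that of the two-sided pooled test of two proportions at 0.05, by exact enumeration, with 2, 4 or 5 of 36 removed per arm.

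| r | d | Spurious difference (percentage points) | Type I error |
|---|---|---|---|
| 32.7% (the article's control rate) | 0 (all 72) | 0 | 0.054 |
| | 5% | 1.7 | 0.058 |
| | 10% | 3.6 | 0.063 |
| | 15% | 5.8 | 0.076 |
| 50% (assumed) | 0 (all 72) | 0 | 0.045 |
| | 5% | 2.6 | 0.050 |
| | 10% | 5.6 | 0.085 |
| | 15% | 8.8 | 0.115 |

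Part of the movement comes from the discreteness of a small-sample test. With 31 per arm and purely random exclusions, the error is 0.050 at 32.7% and 0.056 at 50%. The rest is due to selective removal.

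**The case against.** The best reply is that the Rejection criteria may remove nobody from the analysis. They stand under discontinuation of the intervention rather than under statistical methods, and they end by keeping the records for efficacy analysis. That stands: for that section the supported point is an ambiguity to resolve. The reply does not reach {17b} or {20c}, which have no such closing sentence.

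A reader might infer several stronger things that the text does not support.

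- *Rejection for meeting an exclusion criterion makes incomplete follow-up a ground for removal*, because one exclusion criterion is "Inability to finish the compliance test, judge the efficacy, and have complete data". That criterion is most naturally a judgement at screening, and the rejection item most naturally means ineligible at entry. The rule that does exclude incomplete data is {20c}.
- *Any use of a prohibited drug leads to removal.* Item 5 applies only where efficacy could not be evaluated. That no forbidden drug is named is not a finding, since a condensed article may leave the list to the full protocol.
- *Serious adverse events are the main reason for unblinding.* They are one example among several.
- *Harms are hidden.* Unblinded patients remain in the safety set.

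The illustrations are also deliberately one-sided. At the article's own control rate and 5% or 10% removal, the inflation of the type I error is small. The trial calls itself exploratory, which lowers the stakes but does not justify giving up the randomised comparison on which its efficacy objective rests.

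**Conclusion.** The point holds in this form: the article excludes randomised patients from efficacy for post-randomisation events ({17b}, {20c} and, ambiguously, Rejection item 5), its rules on such patients conflict, and none restores an analysis of all who were randomised.

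Bias is possible, but neither its size nor its direction can be derived from the document. The direction depends on which arm loses its poorer cases. The worst-case figures (about 0.11 or 0.19 SD for loss of the worst 5% or 10% of one arm) rest on normality, one-arm loss and assumed exclusion rates. The HAMD points rest further on an assumed standard deviation. They show that a few patients per arm can matter, not that they will.

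Removing patients who never took a dose, or who were ineligible on data recorded before randomisation, is different in kind and often accepted. The point does not rest on those removals.

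**What to change.** - Define the primary efficacy set as all randomised patients, analysed as randomised. Allow only two exceptions: no dose taken, and ineligibility shown by pre-randomisation data and judged blind. Because of these exceptions, describe it as a modified set.
- Keep every outcome collected, including scores from patients who used other medication or were unblinded early.
- Replace the exclusion in {20c} with one analysis that uses all available post-baseline HAMD scores, for example a mixed model for repeated measures over weeks 1, 2 and 4, adjusted for baseline. This is needed because unblinded patients stop taking part and may have no week-4 score. The model assumes that data are missing at random, which should be stated.
- Move the exclusions in Rejection item 5, {17b} and {20c} to a per-protocol sensitivity set, fixed before first-level unblinding.
- Reconcile the Shedding criteria, the Rejection criteria, {17b}, {18b} and {20c}, so that each patient has one stated treatment in the analysis.

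The cost is amendment wording, one extra sensitivity analysis and possibly a slightly smaller estimated effect. The sample size does not change, and no clinical rule needs to change for this purpose.

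### The separate-analysis rule for dropouts and the removal rule for rejected cases carry no exemption for safety data, so adverse events in patients who leave could fall outside the by-arm safety comparison

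*Protocol article*

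**What the plan says.** All references are to the protocol article.

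- **Rejection criteria (under {11b}).** The lead-in reads "Cases that have been enrolled but meet one of the following should be removed". Item 1 is "Cases were incorrectly diagnosed and incorrectly included" and item 2 is "Met the exclusion criteria", with no time point. On the records of these cases: "Rejected cases should state the reason, and their original medical records should be retained for statistical analysis of efficacy". Safety is not mentioned.
- **Plans to promote participant retention and complete follow-up {18b}.** For subjects who drop out or interrupt, the data are analysed separately before the blind is lifted and "finally are explained separately in the outcome part of this trial". The rule covers the data as a whole and is not limited to efficacy.
- **Shedding criteria (under {11b}), item 4.** Withdrawal because of disease, at the study physician's judgement, counts as dropout.
- **Procedure for unblinding if needed {17b}.** Emergency-unblinded patients are taken out of the efficacy evaluation, but "the data should still be included in the safety analysis data set".
- **Adverse event reporting and harms {22}.** Events during the study go on the case report form, and "cases who discontinue because of adverse effects should be followed up with a detailed record of the handling and outcome".
- **Biological specimens {33}.** The blood and urine tests, which include the safety laboratory tests, are repeated when the patient leaves.
- **Abstract.** Evaluating safety is part of the aim, and the results are to provide evidence on it.

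**The concern.** Patients who leave early are those in whom a harm of treatment is most likely to show. A safety comparison between Xiaoyao pills and placebo is informative only if their events are counted in the arm to which they belong. Two stated rules work against this. One sets the data of dropouts apart before unblinding. The other removes rejected cases and names efficacy as the use of their records. If both are applied to adverse events, the by-arm table describes mainly patients who tolerated four weeks of pills, and a difference in harm could be understated or missed.

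The open wording of rejection item 2 adds to this. Some exclusion criteria, such as those in "Bipolar depression, treatment-resistant depression, and severe suicidal risk", and severe hepatic or renal disease or pregnancy, describe states that can also arise after entry. If the item is applied to them, an on-treatment event could be handled as a question of eligibility and not counted as a harm.

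**Working it through.** **Step 1. Is safety data inside the two rules?** The table sets the provisions side by side.

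| Group | What is done with their data | Safety data exempted? |
|---|---|---|
| Emergency-unblinded ({17b}) | Out of efficacy | Yes, expressly |
| Dropouts and interruptions ({18b}) | Analysed separately before unblinding, reported separately | No |
| Rejected cases ({11b}) | Removed; records kept for efficacy analysis | No |

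The sections on adverse events {22} and specimens {33} govern what is collected. The {18b} and rejection rules govern what is done with it afterwards. Recording an event does not by itself place it in the comparison.

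**Step 2. Can the separate analysis serve as a by-arm analysis?** Under {17b} the first-level unblinding identifies the groups for statistical analysis. An analysis run before any unblinding cannot be split by arm. If {18b} means only before the second level, a split by coded group would be possible, but dropouts would still be analysed and reported apart from the other patients.

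**Step 3. Do patients who leave because of harm fall under {18b}?** Yes, through shedding item 4, which makes withdrawal because of disease a dropout.

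**Step 4. How many patients?** Inputs from Sample size {14}: 30 per arm, 15% dropout, 72 recruited.
- Plan's own figure: 30 / (1 − 0.15) = 35.3, rounded up to 36 per arm; 2 × 36 = 72. Reproduced.
- Expected dropouts: 0.15 × 72 = 10.8 in all, 0.15 × 36 = 5.4 per arm, so about 5 per arm, leaving 36 − 5 = 31.
- The article gives no figure for rejected cases; they would add to this.

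**Step 5. What could be hidden?** The documents give no adverse-event rate, so everything here is assumed. Let each arm have 5 leavers and the same number *c* of completers with an event. Let *a* active and *b* placebo leavers have an event.
- Completers only: *c*/31 in each arm, difference 0.
- All treated: (*c* + *a*)/36 against (*c* + *b*)/36, difference (*a* − *b*)/36.
- With *a* and *b* each between 0 and 5, the hidden difference lies between −5/36 and +5/36, that is ±13.9 percentage points, and is 0 if *a* = *b*.
- Example with *c* = 3, *a* = 4, *b* = 1: completers 3/31 = 9.7% in both arms; all treated 7/36 = 19.4% against 4/36 = 11.1%, a difference of 3/36 = 8.3 points. Fisher's exact test on 7/36 against 4/36 gives p = 0.51.

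**Step 6. Rejection item 2.** Two readings fit the text.
- *Violation at entry:* the item is the exclusion-side counterpart of item 1.
- *Any time:* item 1 already covers wrong inclusion, and no time point is given.

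Nothing in the article settles which is meant.

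**The case against.** The strongest reply is that no section takes dropouts or rejected cases out of the safety set. The set is mentioned once, and its definition is commonly left to the full protocol or the SAP, neither of which is shown. That stands: the lack of a definition is no finding, and none is claimed. The point rests on two rules that the article does state, and on their scope.

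Four stronger readings are tempting, and the documents do not support them.

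- *Only emergency-unblinded patients are in the safety set.* The word still in {17b} presupposes a wider set. These patients are the only ones expressly assigned to it, which is a weaker statement.
- *On-treatment events are rejected as ineligibility.* Item 2 can equally mean a violation at entry. The exclusion on inability to have complete data can be read as a judgement made at entry, so it does not decide the matter. Nor does the item on cases without any test record clearly reach early leavers, since {33} takes blood and urine at baseline.
- *Harms in leavers go without follow-up.* Section {22} requires recording, follow-up and 24-hour reporting of serious events, {21b} sends adverse events immediately to the principal investigator, and {33} repeats the tests at exit.
- *The dropout list has no room for harm.* Shedding item 4 can cover it.

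It is also fair to say that the illustration assumes that leavers' events are left out, that its counts are invented, and that the example is far from statistical significance even with all patients counted. It shows what could be hidden, not what will be.

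**Conclusion.** The point holds in this form: {18b} and the rejection criteria dispose of the data of patients who leave or are removed without exempting safety data, although {17b} shows that the authors make such an exemption where they intend one. Followed as written, adverse events in these patients would be collected but could fall outside the by-arm safety comparison. The timing of rejection item 2 is a separate ambiguity that should be cleared up.

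The size is about 5 of 36 patients per arm, on the protocol's own 15% dropout assumption and with dropout equal between arms. The effect on the adverse-event comparison cannot be computed from the documents; the range of 0 to 13.9 points in either direction assumes 5 leavers per arm, equal event counts among completers, and leavers left out of the table. Severity is moderate: safety is a stated aim and the arms are small, but the data are to be collected and the remedy is wording.

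**What to change.** 1. In Rejection criteria and in {18b}, state that the removal and separate-analysis rules do not apply to safety data.
2. State that every randomised patient who took at least one dose stays in the by-arm safety analysis set, including dropouts, rejected cases and emergency-unblinded patients.
3. Reconcile rejection item 2 with the exclusion criteria, the shedding criteria and {22}: say at which time point the item applies, and make sure that a condition arising on treatment is also recorded and analysed as an adverse event. Who is to be withdrawn or removed is a clinical decision for the trial team; the request is only that these sections agree.

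The changes should be made before unblinding. They use data that the article already requires and need no new visits or tests. The reported adverse-event rate may be somewhat higher.
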